**Intervention**			
	Active comparator	Internet-delivered cognitive behavioral therapy	
**Key inclusion and exclusion criteria**			
	Ages eligible for study	10-17 years	
	Sexes eligible for study	Any	
	Accepts healthy volunteers	No	
	Inclusion criteria	History of any cancer diagnosis, >2 years post treatment or completed treatment and >5 years post diagnosis, pain present over prior 3 months that impairs at least one area of daily life and occurs >1 per month, computer access and literacy.	
Study type			Interventional study; intervention model: single arm; primary purpose: pain management; phase II
Date of first enrollment			May 24, 2022
Target sample size			34
Recruitment status			Currently recruiting
Primary outcomes			Feasibility, satisfaction
Key secondary outcomes			Pain intensity, activity limitations, anxiety symptoms, depressive symptoms, pain interference, insomnia symptoms, parent catastrophizing about child’s pain, parent distress, parent responses to child’s pain behaviors

^a^The funders will not contribute to any aspects of study design or management. The sponsor will be responsible for overseeing the study, interpretation of data, and the decision to submit the report for publication.

### Intervention

Upon completion of the pretreatment questionnaires, survivors will receive access to the WebMAP program, an 8-week web-based cognitive behavioral therapy program with weekly modules including (1) education about chronic pain, (2) recognizing stress and negative emotions, (3) deep breathing and relaxation, (4) implementing coping skills at school, (5) cognitive skills, (6) sleep hygiene and lifestyle, (7) staying active, and (8) relapse prevention.

WebMAP is built using a responsive framework so that it can be easily viewed on any internet-enabled device (eg, smartphone and laptop). The program makes use of multimedia components (eg, audio and video) and interactive exercises. Support is provided through a message center, which allows asynchronous messaging with a coach over the internet. The study coach will be a member of the research team (MP) and is a clinical psychology doctoral student trained in cognitive behavioral therapy. The study coach will have access to a previously developed web-based coach’s manual to standardize responses to participants in the message center. The WebMAP backend system monitors the completion of modules so treatment progress can be recorded.

Survivors will be asked to complete 1 module per week, which is approximately 20 minutes in length. Survivors and parents will be asked to spend approximately 4.5 hours each over the course of the intervention on WebMAP including 4 hours to complete the modules and 30 minutes total corresponding with a coach.

Each week, survivors will be instructed to log in to WebMAP to learn a new skill and practice that skill for 1 week to allow time for skills acquisition. WebMAP consists of 2 separate, password-protected programs including 1 for children and adolescents and 1 for parents.

Parents will also be given access to their own web-based program with weekly modules including (1) education about chronic pain, (2) recognizing stress and negative emotions, (3) operant strategies I (using attention and praise to increase positive coping), (4) operant strategies II (using reward to increase positive coping and strategies to support school goals), (5) modeling, (6) sleep hygiene and lifestyle, (7) communication, and (8) relapse prevention. The parent version of WebMAP uses the same type of multimedia and interactive elements as the teen version including access to the message center.

### Measures

#### Clinical and Demographic Information

We will collect clinical and demographic information from parents including survivor’s date of birth, gender, race, ethnicity, and household income. We will also ask about the survivor’s previous medical issues (excluding cancer) including major injuries, illnesses, or surgeries as well as current or past history of pain treatments (behavioral or pharmacological). Upon receiving consent, we will also collect clinical information from electronic medical records including survivor sex, diagnosis date and description, and treatment received.

#### Objective 1

##### Feasibility

Feasibility will be assessed by considering rates of: (1) recruitment, (2) retention, (3) treatment engagement, (4) acceptability, and satisfaction. “Recruitment” will be measured by the number of survivors enrolled or consented divided by the total number of survivors invited to participate. Based on previous trials of similar nature [17], a 50% recruitment rate of eligible survivors will be used as the benchmark to determine this factor of study feasibility. “Retention” will be measured by the number of survivors who complete the study defined as those who complete the intervention and all assessments from enrollment (T0) to 3-month follow-up (T2) divided by the total number of survivors who enrolled in the study. Survivors will be considered to be enrolled in the study when they have read and signed the informed consent form. Based on previous pilot trials [17], an 80% retention rate will be considered “feasible.” “Treatment engagement” will be measured by number of modules completed by survivors and parents. Based on similar trials [17], the goal to determine treatment engagement will be at least 75% of survivors completed at least 6 of the 8 modules, and the mean number of modules completed by the sample being at least 6. We hypothesize that >75% of survivors will complete assessment measures across the 3 specified time points. “Acceptability” will be measured using the Treatment Evaluation Inventory—Short Form (TEI-SF) [32], a 9-item self-report measure of acceptability of treatment, completed by both survivors and parents. The TEI-SF was originally designed to measure parents’ acceptability of a treatment for children with problem behaviors but has been adapted to assess the acceptability of WebMAP in previous studies [17]. Responses are scored on a 5-point Likert scale and summed to create a total score. Higher scores represent better acceptability. Moderate to high acceptability, defined as a score of 27 or higher, has been considered sufficient for trials of similar nature [17,33]. The TEI-SF has good reliability and validity across various child treatments [32]. This study will use the adapted version and will be completed by survivors and parents.

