### Procedures

#### Recruitment

Survivors will be recruited from the Long-Term Survivors Clinic at the Alberta Children’s Hospital in Calgary, Alberta, Canada. The participant flowchart is in Figure 1. The study team will contact potentially eligible survivors by phone or email. Approximately 700 survivors receive follow-up care at ACH, and an estimated 240 of these survivors may be experiencing chronic pain based on our research [3]. Approximately 94% of Canadians have internet access at home [31] and recruitment rates from our previous pain-related research were 70% [3]. Conservatively, we expect 40% of these survivors to meet our inclusion and exclusion criteria, leaving a possible sample of 70. Meeting our targets would require a participation rate of 49% (34/70).

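### The recruitment rate is calculated over survivors invited, but its 50% benchmark is set for eligible survivors, so the measure and its threshold do not share a denominator

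*Protocol article*

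**What the plan says.** The Feasibility section of the protocol article gives recruitment as the first component of feasibility. It is "measured by the number of survivors enrolled or consented", "divided by the total number of survivors invited to participate". The same section treats signing the consent form as enrolment, so the numerator is clear. The threshold follows directly: "a 50% recruitment rate of eligible survivors will be used as the benchmark".

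The Recruitment section describes who is approached: "The study team will contact potentially eligible survivors by phone or email". It starts from about 700 clinic survivors, of whom an estimated 240 may have chronic pain. It cites 94% home internet access and a 70% recruitment rate in earlier work by the team. It then says that "we expect 40% of these survivors to meet our inclusion and exclusion criteria", gives a possible sample of 70, and derives a required participation rate of 49% (34/70). Table 1 lists feasibility as a primary outcome.

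**The concern.** A threshold can only be applied to a rate that has the same denominator. Here the rate counts everyone invited, while the threshold refers to those who qualify. If some invitees turn out to be ineligible, the rate as defined mixes failure to meet the criteria with unwillingness to take part, and it understates uptake relative to its own benchmark.

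The gap could be large. Criterion 4 concerns recent pain and impairment, which the article only estimates for the clinic population, and it expects fewer than half of some group of survivors to qualify. Two analysts could each follow one of the two sentences and reach opposite conclusions from the same data, and the choice could be made after the counts are known. The Discussion makes a later efficacy trial depend partly on the intervention proving feasible, so the definition matters beyond this report.

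**Working it through.** **Inputs.** From Feasibility: numerator, survivors consented; denominator, survivors invited; benchmark, 50% of eligible survivors. From Recruitment: 700, 240, 94%, 70%, 40%, a pool of 70, and 34/70. From Sample Size: recruitment aim of 38.

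**1. The plan's own figure.** 34/70 = 48.6%, which rounds to the stated 49%. The 70 is what remains after the eligibility criteria are applied, so this planning rate uses the eligible base.

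**2. What the 40% applies to.** The pool of 70 does not follow from the figures given beside it:
- 240 × 0.40 = 96
- 240 × 0.94 × 0.40 = 90.2
- 240 × 0.70 × 0.40 = 67.2
- 240 × 0.94 × 0.70 × 0.40 = 63.2

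700 × 0.25 × 0.40 = 70 does match, but the 25% is the 1-in-4 prevalence from the Introduction, not the 240 used in this section. The group to which the 40% refers is therefore unclear.

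**3. Relation between the two rates.** Let e be the share of invitees who are eligible and u the uptake among eligible survivors. Then

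enrolled / invited = e × u

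The maximum, at u = 1, is e. Reaching 50% of invited requires u = 0.50/e.

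| e | Maximum of enrolled/invited | Uptake among eligible needed for 50% of invited |
|---|---|---|
| 0.40 | 40% | 125% (impossible) |
| 0.50 | 50% | 100% |
| 0.60 | 60% | 83% |
| 0.80 | 80% | 62.5% |
| 1.00 | 100% | 50% |

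The benchmark is unattainable only when e is below 0.50. It is stricter than its wording says whenever e is below 1.

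**4. With the protocol's numbers, if everyone contacted counts as invited.** At e = 0.40 the ceiling is 40% (96/240). Taking the stated pool of 70 against 240 invited, it is 70/240 = 29.2%. Taking 70 against 240 × 0.94 × 0.70 = 158, it is 44.3%. All three lie below 50%.

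**5. One result, two verdicts.** Assume that uptake among eligible survivors equals the 70% recruitment rate of the team's earlier research. At e = 0.40 the rate over invited is 0.40 × 0.70 = 28%, while the rate over eligible is 70%. A milder case is 38 consenting out of 70 eligible, which is 54.3% and passes. At e = 0.80 the same result is 0.80 × 54.3% = 43.4% of invited and fails.

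**6. Eligible base throughout.** 50% of 70 is 35. The planning figure of 34 (48.6%) falls one short, and the recruitment aim of 38 (54.3%) passes. The benchmark is reachable on this base, but the margin is thin enough for the denominator to decide the result.

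**The case against.** A reader might infer that the benchmark cannot be met even if every eligible survivor enrols. The article does not support that as a flat statement. It says that survivors are contacted, and it does not equate contact with invitation. The Discussion mentions screening criteria, and the recruitment flowchart that may show the order of contact, screening and invitation is not available in the text at hand. A clinic could know age and time since treatment before calling anyone. If so, applying the full 40% to those contacted would count the same exclusions twice. The 40% is also described as conservative, and its base is unclear (step 2). Reading invited as meaning eligible survivors who were invited would make the definition, the benchmark and the 34/70 figure agree.

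A reader might also infer that a low rate would cause the trial to be declared infeasible. The article does not say this either. Recruitment is one of several factors, the 50% settles only that factor, and the progression text in the Discussion sets no recruitment cut-off. Nor should 38/240 = 15.8% be taken as a forecast: it assumes that all 240 are invited although recruitment stops at 38.

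These points remove the unconditional claim. They do not remove the mismatch. The coherent reading has to be supplied by the reader, and the definition as written refers to everyone invited.

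**Conclusion.** The mismatch is established from two adjacent sentences and needs no assumption. Its size depends on e, for which the article gives no figure among invitees. At e = 1 there is no effect. At e = 0.8 or 0.6 the uptake needed rises from the stated 50% to 62.5% or 83%. Below e = 0.5 the benchmark is unattainable, and that includes the case where everyone contacted counts as invited and the 40% applies to them. The conclusion is that one component of a primary outcome has a pass mark that does not fit its measure. It does not follow that the benchmark is necessarily out of reach or that the trial would fail on feasibility.

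**What to change.** Define the recruitment rate as survivors who consent divided by survivors screened and confirmed eligible, and apply the 50% benchmark to that rate. This follows the benchmark's own wording and the base of the 34/70 planning figure. Report enrolled over invited as a descriptive proportion without a threshold. If the sponsor already invites only survivors confirmed as eligible, a sentence saying so is enough.

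The cost is about one sentence and a record of screening outcomes. There is one real drawback: survivors who decline before screening have unknown eligibility and drop out of the denominator, which can flatter the rate. Their number should be reported beside it. The article reports 10 participants recruited by December 2022, so the definition should be settled before the rate is calculated. A fuller breakdown of counts, or a sensitivity analysis for early decliners, would be useful but is optional.

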##### Satisfaction

A survey including open-ended questions will be created with patients to elicit feedback on specific modules. These questions will ask about what information was helpful and what may need to be adjusted to better serve youths with a history of cancer for both patients and parents. The satisfaction survey will be completed as part of the posttreatment questionnaire by survivors and parents.

##### Qualitative Interviews

Semistructured interviews will be conducted with survivors and parents separately upon treatment completion to assess feasibility, acceptability, and satisfaction with the program. Patient partners will be involved in creating an interview guide. The interview guide will include open-ended questions about participants’ experience with the program to facilitate self-reflection and open discussion around important aspects of their experience. Interviews will be audio-recorded and transcribed verbatim.

#### Objective 2

##### Pain Intensity

Daily surveys, administered to survivors through REDCap, will be used to assess the daily presence of pain and pain intensity for 7 days at the beginning of each assessment period (T0, T1, and T2). Pain intensity will be assessed with an item asking about the magnitude of pain experienced answered on an 11-point numerical rating scale (0=no pain, 10=worst pain). This measure of pain intensity has demonstrated to be a reliable and valid measure of pain in many populations of children 8 years and older [34-37], including those with chronic cancer pain [38].

##### Activity Limitations

The Child Activity Limitations Interview (CALI-9) [39] is a measure of children’s perceived difficulty in completing typical daily activities because of pain. The CALI will be collected from survivors for 7 days at the beginning of each of the study timepoints (pretreatment, posttreatment, and 3-month follow-up). Survivors will choose from a list of 9 activities (eg, running, doing a hobby, playing with friends, sports, going to school), and will be asked each day whether the activity occurred and how difficult the activity was to perform because of their pain. Total scores range from zero to 100, where higher scores indicate greater functional limitations. Average daily limitation scores across each assessment period will be computed. The CALI has demonstrated reliability and validity in school-age children and adolescents with chronic pain, including those referred to pain clinics from hematology departments [40].

##### Anxiety and Depressive Symptoms and Pain Interference

The Patient-Reported Outcomes Measurement Information System (PROMIS) Anxiety and Depression instruments [41] (8-item short form) will be administered to survivors to screen for current symptoms of anxiety and depression. Survivors will complete the self-report instrument corresponding to their age (child: aged 8-17 years; adult: aged 18 years or older). Items (eg, “I felt worried”) are rated on a 5-point scale (1=never, 5=always). Higher scores signify greater severity of symptoms. Pain interference will be assessed using the 4-item PROMIS interference scale for survivors 8-17 years of age, and the 7-item PROMIS interference scale for survivors over 18 years of age [42]. The PROMIS pediatric measures have been validated for use in pediatric oncology [42].

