## Methods

### Study Design

This study will use a single-arm, mixed methods, pre-post design. Survivors of childhood cancer with chronic pain will participate in an 8-week internet-delivered cognitive behavioral therapy intervention (WebMAP). Assessment questionnaires will be collected before the intervention (T0), immediately following the intervention (T1), and 3-months after intervention completion (T2). Individual interviews will also be conducted upon completion of the intervention.

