#### Eligibility Criteria

Inclusion criteria for participation are (1) history of any cancer diagnosis; (2) current age 10-17 years; (3) >2 years posttreatment or completed treatment and >5 years post diagnosis; (4) pain present over prior 3 months that impairs at least one area of daily life and occurs >1 per month; and (5) computer access, internet, and literacy. Survivors wishing to participate without a parent will not be excluded but will still require parental consent.

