#### Data Collection

Upon enrollment and completion of informed consent, survivors and their parents will complete pretreatment questionnaires (T0) and be given access to WebMAP. Upon treatment completion (T1), survivors and parents will complete the same questionnaire battery plus the Treatment Evaluation Inventory—Short Form [32]. In addition, we will conduct posttreatment interviews to gather feedback on the program. Patient and caregiver partners will be involved in creating the interview questions and conducting a portion of the interviews. Interviews will be recorded and transcribed. Finally, survivors will be administered the same questionnaire battery at 3 months post intervention (T2) to assess longer-term effects of the intervention. Questionnaires will be completed over internet via Research Electronic Data Capture (REDCap) tools hosted by the University of Calgary Clinical Research Unit. REDCap is a secure, web-based application designed to support data capture for research studies, providing (1) an intuitive interface for validated data entry, (2) audit trails for tracking data manipulation and export procedures, (3) automated export procedures for seamless data downloads to common statistical packages, and (4) procedures for importing data from external sources. The investigator leading the trial (MP) and the sponsor (FS) will have access to the final trial data set (Table 1).

**Table 1 table1:** World Health Organization trial registration data set.

Data category			Information
Primary registry and trial identifying number			ClinicalTrials.gov NCT05241717
Date of registration in primary registry			February 4, 2022
Sources of monetary or material support			Alberta Children’s Hospital Trainee Small Research Grant^a^
Primary sponsor			[name]^a^, [contact]
Contact for public queries			[name], [contact]
Public title			Internet-delivered cognitive behavioral treatment for adolescent survivors of childhood cancer with chronic pain
Scientific title			Internet-delivered cognitive behavioral treatment for adolescent survivors of childhood cancer with chronic pain: A pilot feasibility trial
Countries of recruitment			Canada
Health conditions or problems studied			Cancer, chronic pain

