### Data Analysis

#### Quantitative Data Analysis

To address objective 1, we will use frequencies and descriptive statistics to describe recruitment and retention rates, treatment adherence, and acceptability. To address objectives 2 and 3, primary efficacy end points of the study will be calculated as within-person changes in outcome measures using Cohen *d* effect sizes from T0 to T1 and T2. Outcome data will be analyzed using paired samples *t* tests in order to assess changes in outcome variables over time. Treatment effect sizes (Cohen *d*) will be calculated for changes in means, standardized by the pooled SD. All quantitative analyses will be conducted using SPSS (version 27; IBM Corp).

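### The PROMIS form is assigned by age without being held at its T0 version, so a participant who turns 18 on study could change instrument within a paired comparison

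*Protocol article*

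**What the plan says.** All references are to the protocol article.

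- **Form selection** (Anxiety and Depressive Symptoms and Pain Interference): "Survivors will complete the self-report instrument corresponding to their age (child: aged 8-17 years; adult: aged 18 years or older". Anxiety and depression are given one length, 8 items. Pain interference uses the "4-item PROMIS interference scale for survivors 8-17 years of age, and the 7-item PROMIS interference scale for survivors over 18 years of age". Nothing says that the version used at T0 is kept.
- **Entry** (Eligibility Criteria): "current age 10-17 years".
- **Timing** (Study Design): the intervention lasts 8 weeks, and questionnaires are collected before it, "immediately following the intervention (T1), and 3-months after intervention completion (T2").
- **Repetition** (Data Collection): "survivors will be administered the same questionnaire battery at 3 months post intervention (T2"). The same section promises the same battery at T1, and the abstract likewise says that the measures are repeated unchanged.
- **Analysis** (Quantitative Data Analysis): "primary efficacy end points of the study will be calculated as within-person changes in outcome measures", with paired t tests and Cohen d standardized by the pooled SD.
- **Status of these outcomes** (Table 1): anxiety, depressive symptoms and pain interference are key secondary outcomes.

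**The concern.** Nobody can be 18 at entry. An adult form can therefore be reached only by passing an 18th birthday during follow-up. If the rule works as age at assessment, that person answers the pediatric form at T0 and the adult form at T1 or T2, and the planned analysis subtracts one from the other. The difference then mixes real change with the difference between instruments. In a sample of about 34, one or two such values can move a mean change.

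This is a rule about which data are collected. No later analysis plan can recover pediatric-form answers that were never asked for.

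**Working it through.** The article gives no figure on this point. From its sample-size section I take only 34 analysed, 38 recruited (34/0.90 = 37.8) and d = 0.4.

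**1. Which reading gives the rule a use?**
- Age at enrolment: all entrants are 10-17, all receive the child forms throughout, and the adult forms are never used.
- Age at assessment: the adult forms are used for anyone who turns 18 before T1 or T2.

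Only the second gives the adult text a function. The promise to repeat the same battery favours the first but does not settle it, because a battery can have age versions.

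**2. How many would switch?**
- T0 to T1: 56 days / 30.44 = 1.84 months. T0 to T2: 1.84 + 3 = 4.84 months.
- Assumption: ages uniform over the 8 years from 10 up to the 18th birthday (96 months).
- By T2: 4.84/96 = 5.04%; × 34 = 1.7 (× 38 = 1.9). P(at least one of 34) = 1 − (1 − 0.0504)^34 = 0.83; P(at least two) = 0.52.
- By T1: 1.84/96 = 1.92%; × 34 = 0.65. P(at least one) = 0.48.
- Range: 4.84/12 = 40% of 17-year-olds pass 18 by T2. If they are 5% of the sample, 34 × 0.05 × 0.403 = 0.7 switch; if 25%, 34 × 0.25 × 0.403 = 3.4.

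**3. What would a switch do to pain interference?** PROMIS scoring is not stated, so two cases are shown. Both assume two switchers among 34 at T2, true d = 0.40 and pre-post correlation 0.5, and both were simulated with 20,000 trials.

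*Raw sums* (assumed baseline mean 10, SD 4; items scored 1-5 on both forms). The range moves from 4-20 to 7-35, so an unchanged item mean of 1, 2 or 3 adds 3, 6 or 9 points.
- True post mean: 10 − 0.4 × 4 = 8.4. On seven items: 8.4 × 7/4 = 14.7, a spurious rise of 6.3.
- Shift in mean change: 2 × 6.3/34 = 0.37, so −1.60 becomes −1.23.
- The simulation agrees (−1.23). With the pooled SD also somewhat larger, d is about 0.29. One switcher gives about 0.35 and three about 0.25.

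*T-scores* (assumed SD 10; assumed child-adult offset b against improvement).
- b = 2: 2 × 2/34 = 0.12, so −4.00 becomes −3.88 and d is about 0.39.
- b = 10: 2 × 10/34 = 0.59, so −4.00 becomes −3.41 and d is about 0.34.
- The documents do not give the sign of b. If it were reversed, d would be inflated.

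**4. Anxiety and depression.** The article gives one length, 8 items, so the length calculation does not carry over. The child and adult forms are still separate instruments, but no size can be derived.

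**5. The cut-offs.** The adult form starts at 18 or older for anxiety and depression, but the 7-item scale is for those "the 7-item PROMIS interference scale for survivors over 18 years of age".
- In whole years, a 17-year-old entrant is at most 18 at T2, 4.84 months later. Nobody then reaches the 7-item form, and an 18-year-old has no interference form at all.
- If the phrase means past the 18th birthday, the change from 4 to 7 items occurs and there is no gap.

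The two consequences exclude each other, but either way the wording needs correcting.

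**The case against.** The strongest reply is that the text refers to the survivors' age, not to age at each assessment. Together with the promise to repeat the same battery, this may simply be leftover wording from a wider age range, with no switch intended. That is possible, and a switch cannot be stated as certain. It does not remove the point: on that reading the adult and 7-item forms are dead text and should go, and on the other reading the comparison is broken.

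It can also be said that an article commonly leaves PROMIS scoring to the full protocol or analysis plan. That stands. The absence of a scoring rule is no fault here; it only means that the size must be given as a range.

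A reader might go further than the documents allow in three ways:
- **A large loss of power.** In the raw-sum illustration, two-sided power falls from 62% with no switcher to 35% with two. That depends on unstated raw-sum scoring and on an assumed mean, SD and correlation, and it concerns pain interference at T2 only. At T1, no switcher is slightly more likely than one or more.
- **The same artefact in all three PROMIS outcomes.** A change in length is documented for pain interference alone.
- **Both a switch to seven items and a missing form at age 18.** These rest on opposite readings of the cut-off and cannot both be claimed.

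**Conclusion.** The point holds as a flaw in a stated data-collection rule. As written, the rule either moves some participants to a different instrument within a paired comparison or names forms that nobody can use, and it must be reconciled with the promise of an unchanged battery.

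Its reach is limited. One or two participants are expected to be affected by T2 and fewer than one by T1, given uniform ages. Only three secondary outcomes are exposed. Feasibility and satisfaction (the primary outcomes), the pain rating scale, the activity limitation score and the insomnia index are untouched. For pain interference the distortion at T2 runs from slight (d about 0.39) to material (d about 0.29 instead of 0.40), according to scoring that the article does not state; on T-scores its direction is unknown. The correction is worth making because it is almost free and cannot be made after the data are collected.

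**What to change.** In the PROMIS paragraph, replace the age rule with: each survivor completes the pediatric PROMIS anxiety, depression and pain interference forms at T0, T1 and T2, even if they turn 18 during the study. Delete the adult forms and the 7-item scale; this also removes the conflicting cut-offs. No participant then switches.

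Optionally, add a sensitivity analysis that excludes PROMIS assessments made after the 18th birthday. For any adult forms already administered, that exclusion is the remaining remedy.

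The cost is one sentence and a change to the REDCap branching. The downside is small: one or two participants just past 18 answer a form labelled for ages 8-17, for less than five months.
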